### Criteria for withdrawal

The participation will be voluntary, and the participants are free to withdraw from the study at any time any justification and this will in no way affect their future treatment.

Other possible criteria for drop-out/withdrawal are if the participant develops adverse events (AEs), suddenly has abnormal laboratory values, participants develop a condition during the study that violates the inclusion/exclusion criteria, the participant did not proceed to a qualifying operation, enteral and/or parenteral nutrition is administered after surgery, prolong fasting/nil by mouth (NBM) due to any procedure, and particular prescription from a physician that will interfere with the intervention.

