#### Control group, Group NN

Participants in Group NN which is referred to as the control group will receive the standard care of the clinic without getting supplemented with ONS. Nutritional advice will be based on a guideline specifically focused on the treatment of symptoms such as nausea, vomiting, loss of appetite, and diarrhea, and how to deal with the symptoms through nutritional approaches. The advice will be given by clinicians or nurses in the clinic. Those who are identified as having moderate and severe malnutrition will be referred to a dietitian for nutrition counseling. Participants in this group will also have to follow up through phone calls from time to time to assess and monitor their nutritional status before a scheduled surgery. The researcher will attend to any problems faced by participants in this study.

All participants will receive standard postoperative care from clinical and nurse staff with the commencement of free fluids and reintroduction of the normal diet without interference from the researcher or protocol. ONS will be given after surgery, only to the intervention group (Group SS) starting on the first day of nourishing fluid/diet allowance until the day of hospital discharge according to the prescription given. On the other hand, participants in the Group NN would not be given any ONS at postoperatively (Table 2).

**Table 2 Tab2:** ONS allocation

Group	Preoperation	Postoperation
Group 1 (SS)	Supplements	Supplements
Group 2 (NN)	No supplements	No supplements

All participants will have to follow up either at an outpatient clinic or home visit 4 weeks after hospital discharge. Regular (fortnightly) contact with all participants will be maintained for 4 weeks after discharge to monitor their nutritional status and progress. Control groups will be treated exactly as the intervention group apart from the ONS provided.

Participants also will be monitored for complications throughout the study period. Monitoring will occur by daily observation of the participant, checking their medical and nursing notes, and liaising with the attending surgical team and nursing staff. At the same time, complications will be noted as major or minor by using a validated criterion [23].

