### Primary outcome measure

#### Length of hospital stay

Length of hospital stay will be recorded starting from postoperative day 1 until the day of the patient’s discharge. The total length of hospital stay will be taken during visit 2, the day of the patient’s discharge.

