### Analysis of results

The data collected will be analyzed by using the statistical software Statistical Package for Social Sciences (SPSS) and checked for normality via Kolmogorov-Smirnov analysis. All data will be normally distributed as indicated by *p*>0.05 unless otherwise stated. If the data will be not normally distributed, analyses will be carried out on the natural logarithm of the values to improve the symmetry and homoscedasticity of the distribution.

Descriptive statistics, including percentages, mean values, and standard deviations, will be used to describe the baseline demographic data, type of diseases, nutritional status level including anthropometric data, and dietary intake. The median will be used when the data are skewed. When the data become skewed, the mean loses its ability to provide the best central location for the data because the skewed data are dragging it away from the typical values. In addition, the median is not strongly influenced by skewed values.

The values from both groups will be compared using an ANOVA test for approximately normally distributed data, followed by tests on pairs of groups using the Bonferroni adjustment. Non-normal data will be compared by the Kruskal-Wallis test followed by the Mann-Whitney *U* test. ANCOVA or logistic regression will be used with models adjusted according to potential confounders to determine predictors of changes in the key outcome variables of the length of hospital stay with *p*<0.05 significance level. An intent-to-treat (ITT) analysis will be performed to determine the effect of the intervention study on the assumption that participants have adhered to the dietary advice and ONS at the start of the intervention study and had baseline and endpoint values. In other words, ITT analysis includes every randomized subject; according to randomized treatment assignment regardless of their non-compliance, subsequent withdrawal from treatment, or deviation from the protocol and anything that happens after randomization. The effect of intervention between treatment groups on outcome parameters will be carried out by using General Linear Model (GLM) for repeated measure procedure. This method is quite robust to violation of the assumption of normality [33].

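### Withdrawal for postoperative events, with two conflicting intention-to-treat definitions, leaves open whether length of stay is compared in all randomised patients or in an outcome-selected subset

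*Protocol article*

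**What the plan says.** After the participant's right to leave at any time, the Criteria for withdrawal section adds a second list. It opens "Other possible criteria for drop-out/withdrawal are if the participant develops adverse events (AEs), suddenly has abnormal laboratory values" and goes on to a new breach of eligibility, no qualifying operation, "enteral and/or parenteral nutrition is administered after surgery, prolong fasting/nil by mouth (NBM) due to any procedure", and a physician's prescription that would interfere with the intervention. The section does not say whether withdrawal means ending the oral supplement (ONS) or leaving the study, or whether outcomes are still recorded afterwards.

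The primary outcome is defined as follows: "Length of hospital stay will be recorded starting from postoperative day 1 until the day of the patient’s discharge". The Data collection procedure section adds that LOS becomes available only at visit 2.

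Analysis of results describes ITT twice in succession. The first sentence presumes the following: "participants have adhered to the dietary advice and ONS at the start of the intervention study and had baseline and endpoint values". The next says that "ITT analysis includes every randomized subject", and that this applies "regardless of their non-compliance, subsequent withdrawal from treatment, or deviation from the protocol and anything that happens after randomization".

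Three other statements matter here:
- Recruitment: the investigator knows the allocation and the participant does not.
- Sample size calculation: the total of 68 (34 per group) includes a 20% drop-out allowance.
- Control group, Group NN: "Participants also will be monitored for complications throughout the study period", by means that include checking the medical and nursing notes.

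**The concern.** Every item on the second list can arise after randomisation, and the postoperative ones arise while LOS is being counted. Artificial feeding after surgery or a long period without oral intake plausibly goes with a slow recovery and so with a long stay. The Discussion says the therapy is meant to overcome surgical complications. If patients are removed because of such events, the comparison conditions on a step between treatment and outcome, and randomisation no longer protects it.

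The distortion can run either way. If the therapy prevents these events, more long stays are removed from the control arm and a real benefit shrinks. If the events, or decisions to withdraw, are more frequent in the ONS arm, that arm loses its long stays and looks better than it is. The second route is a practical risk: the list is introduced as possible criteria, so there is discretion; the person applying it knows the allocation; and the item on interfering prescriptions bears mainly on the group that receives ONS.

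**Working it through.** **1. Does withdrawal remove a patient from the primary analysis?** The relevant statements, set side by side:

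| Section | Bearing on a withdrawn patient's LOS |
|---|---|
| Criteria for withdrawal | Silent on whether recording continues |
| Length of hospital stay; Data collection procedure | LOS is obtained on the day of discharge, at visit 2; no route is stated for a patient withdrawn earlier |
| Sample size calculation | A 20% drop-out allowance suggests that dropped-out patients give no primary data |
| Analysis of results, first ITT sentence | Excluded if no endpoint value exists |
| Analysis of results, second ITT sentence | Included |

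The last two rows cannot both hold. The two before them lean towards loss of the outcome without settling it.

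**2. The plan's own figure.** Inputs from the Sample size calculation: standardised effect 0.8, power 90%, alpha 0.05, drop-out 20%. With the normal formula n = 2(z_alpha + z_beta)² / d² and a one-sided test, n = 2(1.645 + 1.282)² / 0.64 = 26.8, so 27 per arm. Inflated, 27 / (1 − 0.20) = 33.75, so 34 per arm and 68 in total, as stated. The unstated sidedness is a separate matter. What counts here is that the stated total is consistent with treating drop-outs as lost to the analysis: 0.20 × 34 = 6.8, about seven patients per arm.

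**3. How far could removal shift the result?** The document gives no event rates and no extra stay per event, so both are assumed. Let pC and pT be the proportions with a withdrawal event in the control and intervention arms, L the extra days of stay per event, and d the difference in stay (control minus intervention) that does not act through these events.
- Everyone kept: difference = d + (pC − pT) × L.
- All patients with an event removed: difference = d.
- Shift = −(pC − pT) × L.

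| pC | pT | Shift, L = 5 days | Shift, L = 10 days |
|---|---|---|---|
| 30% | 10% | −1.0 | −2.0 |
| 30% | 20% | −0.5 | −1.0 |
| 20% | 20% | 0 | 0 |
| 20% | 30% | +0.5 | +1.0 |

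A negative shift understates the benefit of the intervention; a positive one overstates it. The largest, 2.0 days, is 2.0 / 3.45 = 58% of the planning difference.

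**4. Partial removal.** Assume stays of 8 days without and 18 days with an event, and event rates of 35% (control) and 20% (intervention).
- Everyone kept: control 0.65 × 8 + 0.35 × 18 = 11.5; intervention 0.80 × 8 + 0.20 × 18 = 10.0; difference 1.5 days.
- Half of those with an event removed: control (0.65 × 8 + 0.175 × 18) / 0.825 = 10.12; intervention (0.80 × 8 + 0.10 × 18) / 0.90 = 9.11; difference 1.01 days.
- All removed: 8 against 8, difference 0. That zero is built in, because this example lets treatment act only through the events.

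Both models remove the same fraction of affected patients in each arm. Unequal removal by an unblinded investigator would shift the difference even with equal event rates, so 0 to 2 days is an illustration and not a bound.

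**The case against.** A reader might infer that the primary comparison will certainly be made in an outcome-selected subset, or that it will favour the supplement. The document supports neither. The criteria are only possible ones. Withdrawal criteria and an analysis of all randomised patients can coexist, and the second ITT sentence keeps everyone. If that sentence governs and LOS is recorded to discharge, there is no selection. A condensed article may also leave collection of data after withdrawal to the full protocol.

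Not every criterion bears on LOS. Adverse events and abnormal laboratory values can occur before surgery, and fasting for a procedure need not be a complication. Scheduled biochemistry is taken at baseline and visit 3, and LOS is known at visit 2, so an abnormal result at visit 3 cannot select on stay.

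All of this stands, and it makes the point conditional. It does not remove it. The two ITT sentences contradict each other in the printed text, which is more than an omission, and an analysis label cannot restore an outcome that was not collected.

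**Conclusion.** The point holds in conditional form. The withdrawal criteria and the ITT text are not reconciled, and the answer decides who enters the primary analysis. If LOS is not collected after withdrawal, or if the condition on adherence and endpoint values governs, the comparison is made in a subset selected by events that plausibly go with a longer stay. The direction of bias is unknown. Its size cannot be derived from the document; the 0 to 2 days in either direction rests wholly on assumed event rates of 10% to 30% and assumed extra stays of 5 or 10 days.

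**What to change.** - Reconcile Criteria for withdrawal with Analysis of results.
- Separate stopping the study product from leaving the study. This needs no rule on when ONS stops, and none is proposed here.
- Obtain LOS and complications from the hospital record for every randomised patient who was operated on, unless consent for data use is withdrawn, and analyse as randomised.
- Delete the condition on adherence and on having baseline and endpoint values from the ITT definition.
- Report randomised patients with no qualifying operation by arm, because a stay counted from the first postoperative day is undefined for them.

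The cost is small: revised wording and some extra record retrieval, from notes that staff already check for complications. Trial status gives recruitment as completed on 31 December 2021, so new wording cannot undo withdrawals already made; LOS for those patients would have to be recovered from the records where consent permits. The estimate will include patients who stopped ONS, which fits the pragmatic aim set out under Design.

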### Data collection procedure

Each participant will be assessed in the clinic/wards during four different sessions (baseline, first, second, and third visits) over the study period (Fig. 2). During the baseline visit, screening and recruitment will be conducted at the surgical clinic, attended by potential participants who have appointments for examination and are in line to get surgery appointments. Potential participants are those who are scheduled to have surgery and meet the inclusion and exclusion criteria. The scheduled project team member will be assigned to approach and inform all potential participants about the study procedures. The patient information sheet and consent form will be given to eligible subjects who have agreed to be recruited for the study. Subjects are allowed to bring back the consent form if they are keen to seek advice from their family members. Agreed and consented participants will be randomly sampled and divided into two (2) groups.

During the baseline visit (pre-study phase), the researcher will be obtaining the patients’ history of dietary intake via 24-h dietary recall. Based on this assessment, the researcher will be able to determine participants’ estimated intake based on their estimated requirements. The dietary advice will be given individually and is structured based on ESPEN guidelines for surgical patients [15].

Participants who are allocated to Group SS will be supplied with ONS, a maximum of 4 servings/day according to their requirements. Participants need to consume the supplied ONS starting from recruitment until 6 h before surgery. Follow-up through phone calls from time to time will be done to assess participants’ compliance with the supplied ONS. During the study phase, participants need to consume ONS once allowed, and compliance will be assessed daily until discharge. Participants will be asked to keep the ONS packaging material during both phases. The researcher will collect the packaging material during the 1st visit and the day of hospital discharge. While Group NN will not be supplemented by any of ONS in the pre-study phase and study phase.

During visits 1, and visit 3, dietary intake data will be collected using a self-administered 2-day 24-h dietary record. All the participants will also be given comprehensive verbal instructions on the method of recording food intake using the 2-day 24-h dietary record. The illiterate participants will be asked to seek assistance from their family members to record for them. They will be asked to complete the 2-day 24-h dietary record of food intake before their next visit, which will be used as the basis for their individualized dietary advice.

During the baseline visit, all data collection will be conducted including a socio-demographic questionnaire, with exception of data for *length of hospital stay* which can only be obtained at visit 2. Meanwhile, anthropometric measurements (except height) and PG-SGA questionnaire, the same methods and instruments will be used repeatedly at visit 1 and visit 3. Data for handgrip will be conducted at every visit while biochemical data will be collected for a second time at the end of the study which is during visit 3. The details of the assessment and procedure are shown in Table 3.

**Table 3 Tab3:** The assessment procedure at (baseline), visit 1, visit 2, and visit 3

The assessment procedure	Visit			
	Baseline	1	2	3
**Questionnaire**				
Social demographic background	/			
The scored PG-SGA	/		/	/
**Dietary assessment**				
1-day 24-h dietary recall	/			
2-day 24-h dietary record			/	/
**Anthropometric measurements**				
Body weight	/		/	/
Height	/			
Mid-arm circumference	/		/	/
Triceps skinfold thickness	/		/	/
**Biochemical data**				
Serum albumin—Medical report	/			/
White blood count—Medical report	/			/
Hemoglobin—Medical report	/			/
C-reactive protein	/			/
**Functional status**				
Handgrip strength	/	/	/	/
**Complications postoperative**				
Length of stay in hospital			/	

### Primary outcome measure

#### Length of hospital stay

Length of hospital stay will be recorded starting from postoperative day 1 until the day of the patient’s discharge. The total length of hospital stay will be taken during visit 2, the day of the patient’s discharge.

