### Study population

Men and women who plan for surgical procedures will be invited to participate in this study with informed consent. A screening form will be used to exclude those who do not meet the inclusion criteria. The inclusion criteria are those who are receiving elective major surgery treatments for gastrointestinal and oncology-related surgery, aged from 18 to 65 years old, Malaysian, able to communicate verbally, Malnutrition Screening Tool (MST) score ≥ 2, and provided and signed informed consent. The exclusion criteria are those who are receiving elective major surgery treatments other than gastrointestinal and oncology-related including bariatric surgery, those who have received preoperative enteral or PN, those who require emergency surgery, complicated with chronic diseases and fluid retention (renal/ cardiovascular/pulmonary/ hepatic), and those who have participated in other research studies.

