### Recruitment

Potential patients who are attending the surgical clinic will be approached by the project team member. They will inform all potential participants of the study procedures. However, the study is single-blinded when the investigator but not the study participants knows which treatment has been allocated. The patient information sheet and consent form will be given to the eligible subjects who have agreed to be recruited for the study. Subjects will be allowed to bring back the consent form if they are keen to seek advice from their family member. The consented participants will be randomized into one of the two groups; either into intervention (SS) or control (NN) group.

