#### Intervention group, Group SS

Group SS will be receiving tailored, more intensive, and ongoing nutrition support and lifestyle advice as compared to Group NN. They will be supplemented with oral nutrition support (ONS), available in 400g/can, providing 226 kcal/serving and 9.6 g protein/serving. ONS will be prescribed according to the patient’s requirement, from 1 to 4 servings a day*.* ONS consumption should be daily from 7 to 14 days until 6 h before the scheduled surgery. Patients are encouraged to consume ONS in a small portion, frequently and in between meals. They also will receive intensive and detailed nutrition counseling at each visit. Nutrition counseling consists of adequate energy and protein according to requirement, fluid and salt intake, replenishment of micronutrients, and controlling blood glucose levels before surgery. Follow-up phone calls will be done from time to time to monitor their progress.

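### A randomised patient who is never operated on has no length of stay, yet the protocol both lists that patient for withdrawal and claims to analyse every randomised subject

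*Protocol article*

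**What the plan says.** All places are in the Protocol article.

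- **Timing of allocation.** Patients are approached at the surgical clinic. Under Recruitment: "The consented participants will be randomized into one of the two groups". For the intervention arm, the section on Group SS adds: "ONS consumption should be daily from 7 to 14 days until 6 h before the scheduled surgery". Allocation, and the start of the supplement in one arm, therefore come before surgery.
- **Primary outcome.** Under Length of hospital stay: "Length of hospital stay will be recorded starting from postoperative day 1 until the day of the patient’s discharge". The Data collection procedure describes this figure as one "which can only be obtained at visit 2", and the outcome section places that visit on the day of discharge.
- **Withdrawal.** Criteria for withdrawal lists, among possible reasons, that "the participant did not proceed to a qualifying operation". It also lists developing a condition that breaches the eligibility criteria. Study population excludes "those who require emergency surgery".
- **Analysis set.** Under Analysis of results: "ITT analysis includes every randomized subject; according to randomized treatment assignment regardless of their non-compliance, subsequent withdrawal from treatment, or deviation from the protocol". The sentence continues to cover any later event. The sentence just before it describes the same ITT analysis differently: it presumes that participants followed the advice and took the supplement at the start, and that they have both a baseline and an end value.

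No section gives a length of stay, or a rule, for a randomised patient who has no operation.

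**The concern.** The outcome exists only after an event that follows randomisation. Some patients may never reach that event, and the protocol itself expects this. For them, the ITT claim cannot be met on the primary outcome, whatever the analyst does.

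Two things are at stake. First, the article supports two different analysis sets, everyone randomised and adherent completers, so the choice could be made after the data are seen. Second, removals happen after allocation. The supplement has begun in one arm, and the Recruitment section says that the investigator knows the allocation. If patients are dropped under a permissive withdrawal list and the result is still called ITT, a selected comparison is presented as a randomised one. For patients who were operated on, this loss is avoidable, because their stay can be counted.

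**Working it through.** **Step 1. Set the rules side by side for each kind of randomised patient.**

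| After randomisation | Postoperative stay exists? | Criteria for withdrawal | ITT, inclusive sentence | ITT, preceding sentence |
|---|---|---|---|---|
| Qualifying elective operation | Yes | No reason arises from the operation | In | In, if adherent with both values |
| Non-qualifying operation | Yes | May be withdrawn | In | In, if adherent with both values |
| Operation became an emergency | Yes | May be withdrawn, if read as breaching eligibility | In | In, if adherent with both values |
| No operation | No | May be withdrawn | In | Out |

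The last row is the conflict proper: the patient must be included, but no value can exist. The two middle rows are a different problem: a value exists, but the withdrawal list may remove it. In every row the two ITT sentences can disagree, because one ignores adherence and the other presumes it.

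**Step 2. Reproduce the planned sample size.** Inputs from Sample size calculation: standardised effect 0.8, difference 3.45 days, power 90%, alpha 0.05, drop-out 20%, 34 per group, 68 in total. The implied SD is 3.45/0.8 = 4.31 days.

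Normal formula: n per arm = 2(z_alpha + z_power)²/0.8².

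- One-sided: 2(1.645 + 1.282)²/0.64 = 26.8, so 27. Then 27/(1 − 0.20) = 33.75, so 34 per arm and 68 in total. This matches.
- Two-sided: 2(1.960 + 1.282)²/0.64 = 32.8, so 33 (34 with the t distribution). Dividing by 0.80 gives 42 (43) per arm, that is 84 (86) in total.

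So 68 fits either a one-sided test with the drop-out allowance or a two-sided t-test without it. Sidedness is not stated, and that is a separate matter. Both are carried forward.

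**Step 3. Effect on power if non-operated patients simply lack the outcome.** The protocol gives no non-operation rate. Its only related figure is the all-cause 20% allowance (0.20 × 68 = 13.6, about 14 patients), so rates up to 20% are assumed. Patients left per arm: n = 34(1 − p). Noncentrality: 0.8 × √(n/2), with 2n − 2 degrees of freedom.

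| Assumed loss p | n per arm | Noncentrality | Power, two-sided t | Power, one-sided t |
|---|---|---|---|---|
| 0% | 34.0 | 3.30 | 90.2% | 94.7% |
| 5% | 32.3 | 3.21 | 88.6% | 93.8% |
| 10% | 30.6 | 3.13 | 86.8% | 92.6% |
| 20% | 27.2 | 2.95 | 82.5% | 89.7% |

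These figures measure lost numbers only. They say nothing about bias if the two arms lose different kinds of patients.

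**The case against.** **The completeness condition already settles it.** A never-operated patient has no end value, so the earlier ITT sentence leaves that patient out. This is true of that sentence, but the next one says the opposite under the same label. It moves the defect into the analysis section and does not remove it.

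**The withdrawal reasons are only possible ones, and the inclusive sentence keeps withdrawn patients.** This is fair for patients with a non-qualifying or emergency operation: an analyst following that sentence would keep them. The article does not say whether withdrawal means stopping treatment or leaving the study, so their retention is not assured.

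**The drop-out allowance covers the loss.** On the one-sided reading it largely does (89.7% at 20% loss). It covers numbers; it does not say who is analysed.

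Several stronger readings are tempting and are not supported:

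- A reader might infer a steep loss of power from entering non-operated patients as zero days. No section proposes that scoring, and the size of the effect would depend on a mean stay that the document does not give.
- A reader might infer that a patient with a non-qualifying operation also lacks the outcome. That patient has a postoperative day 1 and a stay.
- A reader might infer that half of the intervention precedes surgery. The supplement is given before and after, but no split is stated.
- A reader might ask for days in hospital over a fixed window from randomisation, analysed in everyone. A patient who is never admitted would score few or no days, so non-operation would again look like a good result.

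**Conclusion.** The point holds as a contradiction within the article; it is not a detail that could be left to an analysis plan. The outcome definition, the withdrawal criteria and the ITT description cannot all be applied to a randomised patient who has no operation, and the ITT description contradicts itself. The property claimed, a primary analysis of everyone randomised, cannot be delivered for length of stay as defined.

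The loss in numbers is modest: two-sided t-test power of about 87% at 10% loss and 82.5% at 20%, against 90.2% with none. This rests on the planned effect of 0.8, equal loss in both arms, and a non-operation rate that is assumed. Whether bias arises, and in which direction, cannot be judged from the document. The correction is cheap and worth making.

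**What to change.** Reconcile the three sections as follows.

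1. In Analysis of results, delete the condition on adherence and on having both baseline and end values.
2. Define the primary set as all randomised patients who undergo an operation, analysed in the assigned arm. Nobody leaves this analysis because the operation was non-qualifying or became an emergency. This concerns the analysis only and leaves clinical management as it is.
3. Stop describing the primary length-of-stay analysis as including every randomised subject.
4. Report the number not operated on, by arm and with reasons, and do not enter these patients as zero days.

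**Cost.** The wording of two sections and one line in the participant flow. Trial status reports that recruitment is complete, so the change affects analysis and reporting, not conduct; discharge dates for withdrawn but operated patients may have to be taken from hospital records. The trial gives up the full-ITT label for its primary outcome. The new set still conditions on reaching surgery, an event after randomisation that the preoperative part of the intervention could influence, and this should be stated as a limitation.
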